## Abstract

**Background:**

The potential of web-based interventions in dietary behaviour modification of the diabetics has not been fully explored. We describe the protocol of a 12-month match-design randomised controlled trial of a web-based dietary intervention for type 2 diabetic patients with primary aim to evaluate the effect of the intervention on their dietary knowledge, attitude and behaviour (KAB). The secondary objective of this study is to improve the participants' dietary practices, physical measurements and biomarkers.

**Methods/Design:**

A minimum total sample of 82 Type 2 diabetics will be randomised, either to the control group, who will receive the standard diabetes care or the e-intervention group, who will participate in a 6-month web-based dietary intervention in addition to the standard care. The dietary recommendations are based on existing guidelines, but personalised according to the patients' Stages of Change (SOC). The participants will be followed up for 6 months post-intervention with data collection scheduled at baseline, 6-month and 12-month.

**Discussion:**

We are aiming for a net improvement in the KAB score in participants of the e-intervention group, besides investigating the impact of the e-intervention on the dietary practices, physical measurements and blood biomarkers of those patients. The successful outcome of this study can be a precursor for policy makers to initiate more rigorous promotion of such web-based programmes in the country.

**Trial registration:**

Clinicaltrials.gov NCT01246687

## Background

Diabetes is a growing concern in Malaysia and in the world. The prevalence of diabetes in adults worldwide was estimated to rise 366 million in the year 2030 from 171 million in 2000 [1]. The prevalence of Type 2 Diabetes Mellitus (T2DM) in Malaysians above 30 years old was reported to be between 11% and 14% in 2006, and it is estimated to rise further [2]. T2DM accounts for a huge burden of morbidity and mortality through micro and macrovascular complications [3,4]. This has lead to an increasing demand on dietary and lifestyle modifications to delay the disease progression.

Web-based interventions have been successfully implemented in improving self-management of diabetes [5-8], physical activity [9,10] and weight management [11,12] in adults with T2DM. A web-based nutrition education for diabetes prevention study among young adults has shown significant reduction in dietary fat intake [13]. To date there is no published study focused solely on dietary behaviour change in adults with T2DM via a website-based system. Nevertheless, dietary modification has been incorporated as a component of multifactorial behavioural interventions in diabetes prevention and management [11,12,14].

The success of a web-based intervention relies heavily on the website log-in rates, usability, and personalisation. Content development in simplified local language improves the usability of the website [15], while regular reinforcement using reminder services such as e-mails and SMS increases the log-in rates [16]. The use of behavioural theories could assist the personalisation of web-based interventions. Transtheoretical Model (TTM) [17] is one of such behavioural model that has been recently used in web-based interventions, especially those focusing on improving dietary and lifestyle behaviours [10,18].

The study protocol for a randomised controlled trial (RCT) of a web-based dietary intervention for patients with T2DM in Malaysia is presented here. We hypothesised that the e-intervention group will show a greater improvement in dietary KAB than the control group. Secondly, we hypothesised that the web-based intervention to results in a better dietary practices, anthropometric measurements and blood biomarkers in the e-intervention group than the controls.

## Methods/Design

### Study design

This is a two-armed matched-design randomized controlled trial (RCT) scheduled for 12 months (Figure 1). The study is designed according to the recommendations of the CONSORT statement for randomised trials of non-pharmacologic treatment [19].

**Figure 1 F1:**
[figure not shown]
**Flow chart of the proposed study**.

The conceptual framework of the study is presented in Figure 2. Twelve dietary modules in the intervention package is personalised according to the patients' Stages of Change (SOC), and is expected to improve their dietary KAB and assist them to progress in their respective SOC. The improvements in KAB and progress in SOC are expected to be reflected in the patients' dietary practices. Adoption of healthy dietary practices then is expected to be reflected on the anthropometric measurements and biomarkers.

**Figure 2 F2:**
[figure not shown]
**Conceptual framework**.

### Study aims

The primary aim of our study is to evaluate the effect of a six month dietary e-intervention on dietary knowledge, attitude and behaviour (KAB) in patients with T2DM.

The secondary aim is to determine the impact of the intervention on dietary practices (nutrient intake, dietary GI, food frequency score, supplements intake, cooking method and eating out habit), physical measurements (height, weight, body mass index, waist circumference, body fat percentage and blood pressure) and blood biomarkers (fasting blood glucose (FBG), glycosylated haemoglobin (HbA1c) and lipid profile).

### Ethics approval

The study has received ethics approval from Malaysian Ethics Research (NMRR-09-303-3416) and Monash University Human Research Ethics Committee (CF09/1583 - 2009000877).

### Study sample

#### Sample size and power calculation

The sample size calculation is based on a difference in fat and fibre-related behaviour score as reported by a previous computer assisted dietary intervention study in type 2 diabetics [20]. Using a reduction in the mean behaviour score from 1.93 ± 0.5 (baseline) to 1.69 ± 0.4 (post intervention), the GPower software [21] calculated that 31 patients are needed in each group to detect this difference with a two-sided alpha of 0.05, a power of 80%. Based on 30% attrition rate for one year, a minimum of 41 participants are required in each group.

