### Statistical analysis

Axxya Systems Nutritionist Pro™ Diet Analysis is used to analyze the nutrient intakes and all statistical analyses are performed with IBM^® ^SPSS^® ^Statistics 17.0. Independent *t*-test or equivalent is used to determine differences between the study groups for continuous variables, while χ^2 ^or equivalent is used to determine the association between categorical variables. As this is a prospective RCT involving repeated measures, the ANOVA repeated measures model is applied to observe significant differences within the study groups. The evaluation of the intervention is based on an intention-to-treat analysis, with the *p *value 0.05 was taken as the level of significance.

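### The stated 80% power with 31 per group does not follow for a between-group comparison: an unadjusted two-sample t-test on the printed inputs has about 54% power and needs 57 per group

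*Protocol article*

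**What the plan says.** Under Sample size and power calculation, the protocol article takes its effect from an earlier computer-assisted dietary study in type 2 diabetics. The outcome there was a fat and fibre behaviour score, and the effect is a "reduction in the mean behaviour score from 1.93 ± 0.5 (baseline) to 1.69 ± 0.4 (post intervention"). From this the software "calculated that 31 patients are needed in each group to detect this difference with a two-sided alpha of 0.05, a power of 80" per cent. The article then adds: "Based on 30% attrition rate for one year, a minimum of 41 participants are required in each group". The Abstract accordingly gives a minimum total of 82.

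The Background sets a comparison between arms: "We hypothesised that the e-intervention group will show a greater improvement in dietary KAB than the control group". Under Statistical analysis, an independent t-test or equivalent "is used to determine differences between the study groups for continuous variables", and repeated-measures ANOVA is assigned to differences within the groups. The same section says that the evaluation is by intention to treat.

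The sample-size paragraph names no test, no correlation, no expected change in controls and no between-group difference.

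**The concern.** The inputs describe how one set of patients changed from before to after an intervention. The trial asks whether one arm improves more than another. These are different quantities with different standard errors: a between-group contrast carries sampling error from two independent groups. Using the within-arm change as the between-arm difference also assumes that controls do not change at all.

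The figure of 31 is far below what a two-sample calculation on these inputs gives. The 80% figure is the only justification for the total of 82, and readers will use it to judge what a non-significant primary result means. If the real power is nearer to one half, such a result says little.

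**Working it through.** **Inputs (Sample size and power calculation).** Means 1.93 and 1.69, so the difference is 0.24. SDs 0.5 (baseline) and 0.4 (post intervention). Two-sided alpha 0.05, power 80%. Stated n = 31 per group. Attrition 30%, 41 per group randomised. Results below use the noncentral t distribution.

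**Step 1. Try to reproduce 31 with a two-sample t-test.**

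Pooled SD = √((0.5² + 0.4²)/2) = √0.205 = 0.453. Standardised difference d = 0.24/0.453 = 0.530.

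| SD used | d | n per group for 80% power, two-sided | n per group, one-sided |
|---|---|---|---|
| pooled 0.453 | 0.530 | 56.8 → 57 | 45 |
| 0.5 | 0.480 | 69.1 → 70 | 55 |
| 0.4 | 0.600 | 44.6 → 45 | 36 |

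No row gives 31, even if the stated two-sided alpha is set aside.

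**Step 2. Try a paired t-test.** SD of the difference = √(0.5² + 0.4² − 2·r·0.5·0.4) = √(0.41 − 0.4r). The article gives no r, so it has to be assumed:

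| assumed r | SD of difference | n |
|---|---|---|
| 0.3 | 0.539 | 42 |
| 0.4 | 0.500 | 37 |
| 0.5 | 0.458 | 30.6 → 31 |
| 0.6 | 0.412 | 26 |

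At r = 0.5, 0.24/0.458 = 0.524 and n is exactly 31. So 31 can be reproduced, but only with an unstated correlation of about 0.5.

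**Step 3. Power of an unadjusted two-sample t-test at the planned size.** The between-group difference is taken as 0.24, with controls unchanged. After the stated attrition, 41 × 0.7 = 28.7, or 28 to 29 per group.

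| analysed per group | pooled SD 0.453 | SD 0.5 | SD 0.4 |
|---|---|---|---|
| 28 to 29 | 50 to 51% | 42 to 44% | 60 to 61% |
| 31 | 54% | 46% | 64% |
| 41 (all randomised) | 66% | 57% | 77% |

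No cell reaches 80%.

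**Step 4. Difference detectable with 31 per group.** 80% power needs d of about 0.72, and 0.72 × 0.453 is about 0.33 points.

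**Step 5. What baseline adjustment would give.** Residual SD = 0.453·√(1 − r²), difference 0.24, 31 per group:

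- r = 0.5: SD 0.392, power 66%
- r = 0.6: SD 0.362, power 73%
- r = 0.7: SD 0.323, power 82%

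**The case against.** **Origin of 31.** A reader might infer that 31 came from a before-after paired calculation. The inputs are before-after and r = 0.5 matches exactly, but the article names only the software. Other routes also give 31. A between-factor repeated-measures calculation (two groups, three measurements, f = 0.530/2 = 0.265, correlation 0.3) gives 62 in total, or 31 per group. A two-sample t-test on change scores does so at r = 0.75, where the SD is √(0.41 − 0.3) = 0.332 and d = 0.24/0.332 = 0.72. Each route rests on a correlation that the article does not state, so the origin cannot be established. The repeated-measures route also fits this trial poorly, because it averages in a baseline at which no difference is expected.

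**Matched design.** The trial is described as matched, so 31 might mean 31 matched pairs. That would need a correlation of about 0.5 between different people matched on age, sex and ethnicity. The article gives no such figure, takes its inputs from before and after rather than from matched partners, and describes no matched-pair analysis.

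**The test is not fixed.** This stands in part. The article says independent t-test or equivalent for continuous variables in general. It does not tie that test to the primary score or say whether it is applied to final scores or to change, and an analysis plan may settle this. With change scores and 31 per group, power is 53% at r = 0.5, 62% at 0.6, 73% at 0.7 and 87% at 0.8. So 80% is attainable with some analyses, but only with a high correlation that is nowhere stated.

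**Forty-one, not 31, are randomised.** Under intention to treat, all 41 might be analysed. This is fair and raises power to 66% (77% with SD 0.4), still short of 80%.

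**Borrowed inputs.** A reader might conclude that the trial has roughly even odds of detecting its planned effect on dietary knowledge, attitude and behaviour (KAB). The article does not support that: 0.24 and its SDs belong to another study's fat and fibre behaviour score, and no effect or SD is given for the KAB questionnaire. The 54% is the power for the printed inputs, not for the primary outcome itself.

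**Conclusion.** The concern holds as an error in the stated power. The printed means, SDs, alpha and power do not give 31 per group for an unadjusted two-sided two-sample t-test. With the pooled SD, 57 are needed and power at 31 is about 54%, some 26 percentage points below the claim. Over the SDs printed in the article, power with 31 evaluable runs from 46% to 64%.

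These figures assume that the between-group difference equals 0.24, that controls do not change, that scores are compared without baseline adjustment, and that the borrowed SDs apply. Improvement in controls would lower power; a baseline-adjusted analysis with a strong correlation would raise it. The conclusion does not depend on how 31 was obtained, which remains unknown.

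**What to change.** Delete the claim that 31 per group gives 80% power and restate the paragraph for the between-group comparison, in one of two ways:

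- For an unadjusted two-sample t-test: 31 evaluable per group gives about 54% power for a difference of 0.24 (pooled SD 0.453), or 80% power for about 0.33 (d = 0.72).
- For a baseline-adjusted primary analysis: name it, and give its power with the assumed baseline correlation (31 per group: 66% at r = 0.5, 73% at 0.6, 82% at 0.7).

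In either case, name the test and any correlation used. Say that the inputs come from another study's fat and fibre behaviour score, and that using 0.24 as the difference assumes no change in controls.

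The cost is one reworded paragraph and a less favourable stated power. The correction itself requires no extra patients.

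### The 41 per group (82 in total) does not leave the required 31 per group after the plan's own 30% one-year attrition; it covers losses only up to about 24%

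*Protocol article*

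**What the plan says.** The section Sample size and power calculation of the Protocol article starts from a published "reduction in the mean behaviour score from 1.93 ± 0.5 (baseline) to 1.69 ± 0.4 (post intervention"). It reports that the software "calculated that 31 patients are needed in each group to detect this difference", "with a two-sided alpha of 0.05, a power of 80"%. It then allows for loss: "Based on 30% attrition rate for one year, a minimum of 41 participants are required in each group". The Methods/Design part of the abstract repeats the result as a total: "A minimum total sample of 82 Type 2 diabetics will be randomised", with "data collection scheduled at baseline, 6-month and 12-month". The article prints no formula for the attrition step and gives no other provision for lost patients.

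**The concern.** An attrition allowance should ensure that, after the expected loss, the number still evaluable is at least the number the power calculation asked for. Attrition is a fraction of those randomised, so the evaluable number is divided by the retention rate. Adding 30% to the evaluable number gives too few, because the 30% is later lost from the larger, inflated number.

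The article prints the base number, the attrition rate and the inflated number, so consistency can be checked directly. If the inflated number is too small, a trial that recruits exactly to its stated minimum, and loses exactly what it expected to lose, falls below its own evaluable target and its own stated power. The sample size appears in both the abstract and the methods, and readers will use it to judge whether the trial is adequate.

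**Working it through.** **Inputs from the Protocol article.** Evaluable number 31 per group; attrition 30% over one year; inflated number 41 per group, 82 in total; means 1.93 and 1.69 with SDs 0.5 and 0.4; two-sided alpha 0.05; power 80%.

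**1. Reproducing the 41.**
- Multiplying by one plus the attrition rate: 31 × 1.30 = 40.3, rounded up to 41. This matches.
- Dividing by retention: 31 / 0.70 = 44.3, rounded up to 45. This does not match.

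The multiplication is therefore the likely origin of 41, but this is an inference. The next steps do not depend on it.

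**2. What 41 leaves.**
- Per group: 41 × 0.70 = 28.7, that is 28 or 29, against 31.
- In total: 82 × 0.70 = 57.4 against 2 × 31 = 62, a shortfall of 4.6.
- Largest attrition that still leaves 31: 1 − 31/41 = 0.244, or 24.4%.

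**3. What would be enough for this step.**
- 44 per group: 44 × 0.70 = 30.8, still short.
- 45 per group: 45 × 0.70 = 31.5, sufficient. Total 90, which is 8 more than 82.

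**4. Effect on power, paired model.** The 31 is reproduced by a before/after paired t-test if the correlation between baseline and post-intervention scores is 0.5. That correlation is an assumption and is not in the document.
- SD of the change: √(0.25 + 0.16 − 2 × 0.5 × 0.5 × 0.4) = √0.21 = 0.458.
- Standardised change: 0.24 / 0.458 = 0.524.
- The required number depends strongly on the assumption: 37 at a correlation of 0.4, 31 at 0.5, 26 at 0.6.

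**5. Effect on power, two-group t-test.** The same means and SDs are used as if they were two independent groups.
- Pooled SD: √((0.25 + 0.16)/2) = 0.453; standardised difference 0.24 / 0.453 = 0.530.
- 80% power needs 57 evaluable per group. Dividing by retention, 57 / 0.70 = 81.4, so 82 *per group*, which should not be confused with the plan's 82 in total.

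Power from the noncentral t distribution, two-sided 0.05:

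| Evaluable n | Paired model, correlation 0.5 (n patients) | Two-group t-test (n per group) |
|---|---|---|
| 31 | 80.6% | 53.7% |
| 29 | 77.7% | 51.0% |
| 28 | 76.2% | 49.5% |

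Under either model the attrition step costs about 3 to 4 percentage points. With 45 evaluable per group and no loss at all, the two-group test would have 70.1%.

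**The case against.** **The number is only a minimum.** The plan does not cap recruitment at 82, and a larger intake would remove the shortfall. But a stated minimum is the number claimed to be sufficient, and this one is not.

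**The shortfall may not arise at 6 months.** The 30% is a one-year figure, while the primary aim concerns a six-month intervention and there is a 6-month assessment. If loss were constant over time (an assumption), 6-month attrition would be 1 − √0.70 = 16%, leaving about 34 of 41, above 31. If all loss came early, 28.7 would remain. The document gives no 6-month rate. This limits the consequence, but the sample size statement itself ties 41 to one year, and the Discussion looks for improvement when the trial ends. At that time point the error stands.

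**Intention-to-treat analysis keeps everyone.** The Statistical analysis section does commit to intention to treat. Yet the plan inflates for attrition, which makes sense only if lost patients are expected to contribute no outcome data. The allowance, once made, has to be computed correctly.

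**The loss is small.** This stands: about 4 to 5 evaluable patients in total and 3 to 4 points of power. A reader might infer from the mismatch that the attrition step alone leaves the trial seriously underpowered. The figures do not support that. The low two-group power (54% even at 31) comes from the base calculation and not from this step.

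**Replacing 41 by 45 could mislead.** This also stands. A reader might take 45 and 90 as a sound sample size. That holds only if 31 is the right base. The Statistical analysis section names an independent t-test for group differences, for which about 57 evaluable per group would be needed on the same figures. If matched pairs were analysed as pairs and members dropped out independently (both assumptions; no paired test is named), 45 pairs would leave about 45 × 0.49 = 22 intact.

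**Conclusion.** The point holds as an error in a stated figure. With 31 required and 30% lost over one year, 41 per group leaves 28.7; the total is about 57 against 62, and the stated size covers at most 24.4% attrition. These results use only printed numbers. That the plan multiplied by 1.3 is a strong inference, not something the document says.

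Severity is moderate. Power falls from 80.6% to about 76–78% under the paired model, which rests on an assumed correlation of 0.5, and from about 54% to 50–51% for a two-group t-test on the same means and SDs. The conclusion concerns the attrition step alone. Whether 31 is a proper base for the between-group comparison is a separate and larger question, which correcting this step does not answer.

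**What to change.** Make the three figures agree, in both the sample size section and the abstract, in one of two ways.

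- **Keep 41 and 82.** State that at 30% one-year attrition they leave 28 to 29 evaluable per group and that they cover attrition only up to 24%. Give the power at that number, and name the test, the correlation if a paired model is used, and the time point. This costs no patients, only a less favourable stated power: slightly so under the paired model, but about 50–51% if the two-group test is the one named.
- **Print 45 and 90**, showing 31 / (1 − 0.30) = 44.3, rounded up. This means recruiting 8 more patients, about 10% of 82, across the three hospitals.

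In either case, add that the correction concerns attrition only and is conditional on 31 being justified for the planned comparison.

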#### Recruitment process

The eligibility screening, recruitment of study participants and data collections are conducted in the outpatient medical clinic of three urban hospitals in Malaysia. Diabetic nurses provide assistance in identifying potential study participants according to the eligibility criteria (Table 1). If the patients are found have potential to participate in the study, they complete the baseline questionnaire after giving a written informed consent. They are, however, excluded if the baseline dietary KAB score was more than 50%.

**Table 1 T1:** Eligibility criteria

Inclusion	Exclusion
Mentally sound men and women who are ≥ 18 years old. Literate with a fair command of English and/or Malay languages. Have access to the Internet at home, work or public place. Willing to access the study website at least once every fortnight. Have been confirmed of having HbA1c of ≥7.0%.	Pregnant, lactating or intend to become pregnant during the study period. Diagnosed with Type 1 Diabetes Mellitus (T1DM) or Gestational Diabetes Mellitus (GDM) Weighing more than 150% of the desired weight for height. Any pre-existing condition compromising the quality of life or ability to participate according to protocol. Have severe complications (chronic heart disease, cerebrovascular disease, diagnosed HIV/AIDS, cancer, emphysema, chronic liver or kidney disease) that would affect the subjects' ability to follow the tailored advice. Enrolled in other clinical studies. Having dietary KAB score more than 50% at baseline.

### Randomisation and treatment allocation

Eligible diabetic patients who have consented to participate are matched for age, sex and ethnicity, and randomised to either e-intervention or control group.

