#### Control group

This group receives the usual standard treatment (diabetic control and management) given to patients with T2DM. Although the controls have access to the Internet, they receive neither website log-in information, nor any reinforcement via e-mail or SMS.

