#### e-Intervention group

This group receives an intensive dietary intervention through the study website, personalised according to the participants' SOC, in addition to the usual standard treatment at the outpatient clinics.

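### Three hospitals recruit, but hospital is neither a stated matching factor nor in the named between-group tests: a minor loss of balance and precision, cheap to remove

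*Protocol article*

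**What the plan says.** - **Sites.** Recruitment process: screening, recruitment and "data collections are conducted in the outpatient medical clinic of three urban hospitals in Malaysia".
- **Allocation.** Randomisation and treatment allocation: patients "are matched for age, sex and ethnicity, and randomised to either e-intervention or control group". The article calls the trial a matched-design RCT, and this sentence is its whole account of how the matching is done.
- **Size.** Abstract: "A minimum total sample of 82 Type 2 diabetics will be randomised". Sample size and power calculation: at least 41 per group.
- **Background care.** Both arms receive usual treatment. The e-intervention arm gets its programme "in addition to the usual standard treatment at the outpatient clinics".
- **Measurement.** The primary KAB questionnaire is validated and interviewer-administered, by trained enumerators in clinical settings (Outcome assessments; Primary outcomes). Glucose, HbA1c and lipids are taken from the medical record (Secondary outcomes).
- **Analysis.** Statistical analysis names an independent t-test and a chi-square test (or equivalents) between groups, and repeated-measures ANOVA for change within groups. None is described with a hospital term.

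**The concern.** The sponsor chose to restrict the randomisation and named the factors used. Hospital is a natural factor in a three-centre trial, and it is left out. As the rule reads, the two members of a pair may come from different hospitals, and the two arms may end up with different hospital mixes.

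If outcome levels differ between hospitals, for whatever reason, two things follow. An uneven split moves the observed arm difference by a chance amount that the design could have prevented. And variation between hospitals stays in the error term of an unadjusted test. The biomarkers are the most exposed, because their values come from medical records and the article describes no central assay.

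An analysis plan could add a hospital term later. It could not change how the pairs were formed.

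**Working it through.** The article gives no figure on hospital balance, so there is none to reproduce. It also gives no patient numbers or outcome data by hospital. Site sizes and site differences below are therefore assumptions, shown over a range.

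**Inputs from the article**
- 82 patients, 41 per arm, 3 hospitals.
- Planning values "1.93 ± 0.5 (baseline) to 1.69 ± 0.4 (post intervention"), used here only as a yardstick: difference 1.93 − 1.69 = 0.24; pooled SD = √((0.5² + 0.4²)/2) = 0.453; effect = 0.24/0.453 = 0.53 SD.

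**Assumptions**
- Hospital sizes 28/27/27 (or 41/26/15).
- Within-hospital SD = 1, with hospital means at 0, 0.5 and 1 (a span of 1 SD) or at 0, 0.25 and 0.5 (a span of 0.5 SD).
- Allocation independent of hospital. If age, sex or ethnicity is related to hospital, the existing matching balances hospital in part and the figures shrink.

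**Step 1: how uneven the mix can be.** Splitting 82 patients at random into 41 and 41, the chance that at least one hospital differs between arms by 7 or more patients (for example 17 against 10) is about 30% for 28/27/27 and about 26% for 41/26/15. The chance that some hospital's share differs by at least 10 percentage points is 46 to 58% over site sizes from 55/17/10 to 28/27/27. For 20 points it is 7 to 13%.

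**Step 2: what this does to the standard error.**
- Patient-to-patient part: √(2/41) = 0.221 SD.
- Hospital part: √(S² × 2/41), where S² is the variance of the hospital means over the 82 patients. For 28/27/27 and a 1 SD span, S² = 0.170, giving √(0.170 × 2/41) = 0.091 SD.
- Combined: √(0.221² + 0.091²) = 0.239 SD, and 0.239/0.221 = 1.08.

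| Site sizes | Span of hospital means (assumed) | Hospital part (SD) | Combined SE (SD) | Rise |
|---|---|---|---|---|
| 28/27/27 | 1 SD | 0.091 | 0.239 | 8% |
| 28/27/27 | 0.5 SD | 0.045 | 0.225 | 2% |
| 41/26/15 | 1 SD | 0.085 | 0.237 | 7% |
| 41/26/15 | 0.5 SD | 0.042 | 0.225 | 2% |

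**Step 3: validity.** In simulated trials with 41 per arm and hospital ignored in both allocation and test, the two-sided type I error was 4.9 to 5.2% at spans of 0, 0.5 and 1 SD. A separate simulation with 31 per arm and an assumed hospital intraclass correlation of 0 to 0.10 gave 4.7 to 5.7%.

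**Step 4: power for a 0.53 SD effect, with all 41 per arm observed.**
- Span 1 SD: about 58 to 61% ignoring hospital, against about 64 to 66% with hospital in the model.
- Span 0.5 SD: about 64 to 65% either way.
- Span 0: the hospital term costs about 1 point.

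These are relative comparisons, not a check of the planned 80%.

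**The case against.** The strongest answer is that randomisation already deals with this. Any difference in hospital mix is a chance one, and the standard error of the t-test already includes it. That stands in full. A reader might infer a biased comparison or an invalid test, and step 3 shows neither.

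A reader might also infer that a site imbalance could account for a third of the planned effect. The arithmetic exists: 2 × 0.091 = 0.18 SD, against 0.53 SD. But it needs roughly a 1-in-20 imbalance on top of an assumed 1 SD span between hospitals, and it leaves out that ordinary sampling error is already 0.221 SD. The rise in the standard error is the fairer measure.

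A third tempting reading is that usual care is undefined and varies by clinic. The article does not support it. Controls are described thus: "This group receives the usual standard treatment (diabetic control and management) given to patients with T2DM". Both arms receive that care, and nothing says that care, interviewing or laboratories differ between hospitals. An article commonly leaves the content of usual care to the full protocol. For the primary outcome, the enumerators are trained and blinded, and nothing ties them to one hospital.

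Finally, an article may condense the allocation procedure, and the full protocol may already pair within hospital. That is possible, and it keeps the severity low. It does not remove the point: the article names its matching factors, and hospital is not one of them.

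**Conclusion.** The point holds as a minor design weakness. Three hospitals recruit, the stated matching factors omit hospital, and the named between-group tests do not use it, so the arms can differ by chance in hospital mix. There is no bias and no inflation of the type I error.

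The cost is avoidable imbalance and, only if hospitals differ, some precision: about 7 to 8% on the standard error for an assumed 1 SD span of hospital means, about 2% for 0.5 SD, and nothing if hospitals do not differ. The biomarkers taken from medical records have the most to gain. The size rests on assumed site sizes, assumed site differences and allocation independent of hospital.

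**What to change.** - Form the age, sex and ethnicity pairs within hospital and say so in the allocation section. Among complete pairs this makes the difference in hospital mix zero.
- Where no match exists within a hospital, loosen the age match, or allocate by minimisation with a random element that includes hospital alongside age band, sex and ethnicity.
- Include hospital as a fixed effect in the between-group comparisons of KAB and the biomarkers.
- If pairs are already formed within hospital, one sentence saying so settles the allocation part.

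Cost: somewhat looser age matching, since each hospital has a smaller pool. Any patients allocated by minimisation leave the strict paired design, so the procedure has to be written out and not merely reworded. The model spends two degrees of freedom, which costs about 1 to 2 points of power if hospitals do not differ. No extra patients are needed.
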